# Improving Diet Quality of People Living With Obesity by Building Effective Dietetic Service Delivery Using Technology in a Primary Health Care Setting: Protocol for a Randomized Controlled Trial

**DOI:** 10.2196/64735

**Published:** 2025-04-30

**Keywords:** obesity, diet, diet quality, digital behavioral interventions, health behavior change, mHealth, mobile health, eHealth, mobile food record, telemedicine, weight management, obese, RCT, randomized controlled trial, Australia, adult, nutrition, dietitians, access, dietary management, intervention, digital health

## Abstract

**Background:**

Almost a third of Australian adults are living with obesity, yet most cannot access medical nutrition therapy from dietitians, that is, the health professionals trained in dietary weight management services. Across the health system, primary care doctors readily identify people who may benefit from weight management services, but there are limited referral options in the community. Dietitians are trained to provide evidence-informed dietary treatment of overweight and obesity but are underutilized and underresourced. The chat2 (Connecting Health and Technology 2) trial will test combining new technologies for dietary assessment with behavior change techniques to improve outcomes for people living with obesity.

**Objective:**

This study aimed to compare the effectiveness of a 1-year digital dietary intervention, with standard care on body weight reduction and improved diet quality, in adults living with obesity delivered by dietitians in a primary care setting.

**Methods:**

This randomized controlled trial will compare a 1-year, digitally tailored, feedback dietary intervention with a control group in 430 adults living with obesity (BMI≥30 to ≤45 kg/m^2^). Participants will be recruited by letters sent to individuals randomly selected from the electoral roll and supplemented by hospital site posters, newsletters, and unaddressed mailbox delivery postcards sent to residential street points. The primary outcome is change in body weight, measured face-to-face at a baseline, 6 months, and 12 months. A 4-day, image-based dietary assessment tool (mobile Food Record) will be used to measure diet quality score. Secondary outcomes include diet quality score; dual-energy absorptiometry body composition; and total cholesterol, triglyceride, low-density lipoprotein, high-density lipoprotein, glycated hemoglobin, and fasting glucose levels. The intervention group will receive 8 video counseling sessions with a trained dietitian delivered over 12 months to support dietary behavior change and relapse prevention. The trial is unblinded. Both groups will receive feedback on their clinical chemistry and dual-energy absorptiometry scans at each time point.

**Results:**

Participant recruitment commenced in July 2023 and ended in August 2024. Data analysis will commence in 2025, with the anticipated publication of results in 2026.

**Conclusions:**

If found to be effective, the results of this randomized controlled trial will support the delivery of effective, evidence-based weight management advice using new technologies. Improving community access to high-quality dietetic services will ensure more effective use of the dietetic workforce to improve outcomes for people living with obesity.

**Trial Registration:**

Australian New Zealand Clinical Trials Registry ACTRN12622000803796; https://anzctr.org.au/Trial/Registration/TrialReview.aspx?id=383838

**International Registered Report Identifier (IRRID):**

DERR1-10.2196/64735

## Introduction

The high and increasing prevalence of obesity across the world is a major challenge for health care delivery and confers a substantial burden on individuals and the health care sector. The effects of obesity are widely recognized as one of the leading health concerns, affecting all age and socioeconomic groups [1]. For example, in Australia, overweight and obesity and dietary risks collectively account for nearly half of the 38% of the preventable burden of disease, with overweight and obesity being the leading contributor to nonfatal burden [2]. In tandem, direct health care costs associated with obesity-related conditions, such as cardiovascular disease, respiratory disease, type 2 diabetes, and some cancers, are rising with an unequal distribution corresponding to the level of socioeconomic disadvantage [3,4]. Almost a third (31%) of Australian adults are living with obesity, yet most are unable to access weight management services. An urgent priority for health service delivery is to identify the most cost-effective approach to delivering evidence-based weight management.

Primary care is a critical component of addressing obesity and requires a person-centered approach to treatment [5]. This includes changing the weight-stigmatizing narrative among health professionals working with people living with obesity [6]. Treatment guidelines for obesity are evaluated by the person’s BMI and the severity of obesity-related complications [5]. Intensive interventions involving very low-energy diets, pharmacology, or bariatric surgery are indicated with BMI≥40 kg/m^2^ and obesity-related complications [5]. Whereas, for people with BMIs between 30 and 40 kg/m^2^ without complications, supervised lifestyle interventions to achieve 10% initial weight loss are recommended [5]. However, unfortunately in Australia, there are limited referral options for weight management in the community. Publicly supported bariatric surgery waiting lists are long and triaged to those with a BMI≥40 kg/m^2^ with obesity-related complications, and while recently pharmacological treatments have been increasingly used in the treatment of obesity [7], issues with availability and cost limit the access to these pharmacological treatments. In addition, not everyone has access to or wishes to choose the pharmacological pathway. Therefore, continued research on behavioral lifestyle interventions is needed as they remain the first-line treatment for people living with obesity [7].

Lifestyle modification is a fundamental component of weight management. The most effective interventions to date have used behavioral strategies to support people to achieve energy reduction [8]. Guidelines for comprehensive weight management interventions identify the importance of personal counseling to achieve a clinically significant 5% weight loss to confer health benefits, including lowering blood pressure or delaying progression to type 2 diabetes [9]. In a review of primary care interventions for obesity, intensive counseling (≥12 sessions per year), delivered face-to-face, by phone, or electronically, produced weight loss of 4-7 kg, compared with low-dose counseling (≤12 sessions per year) without behavioral strategies, which only resulted in only modest losses of 1-2 kg [8], supporting the value of higher intensity behavioral interventions.

Behavioral interventions for weight management are complex and may include a range of components and modes of delivery. Factors associated with greater effectiveness include changes in diet, provision of meal replacements, and whether the program was delivered by a dietitian or psychologist [10]. A systematic review of weight management interventions demonstrated that those provided by a dietitian resulted in improvements in BMI and other cardiometabolic outcomes compared with control conditions [11]. Behavioral strategies of these weight management interventions, however, were not explored. Teasing out the behavioral components of interventions is important to discover the most effective behavior change techniques. In a review of behavioral interventions in type 2 diabetes, frequent feedback and support were associated with weight reduction [12].

To date, few studies have examined the combined effectiveness of behavior change techniques with new cutting-edge digital technologies and medical nutrition therapy. Digital technologies are effective in supporting weight loss, particularly when combined with personalized feedback [13]. One of the challenges for dietitians in working with individuals living with obesity is the ability to easily and accurately assess diet and dietary behaviors—an important component of personalized advice. Another consideration is people’s willingness to record their dietary intake. An image-based dietary record app with time and date stamp data, termed the mobile food record (mFR), has been shown to be feasible for dietary assessment and feedback, a key component for changing dietary behaviors [14,15]. The content of the images is confirmed either by the participant or by novel automated methods using computer vision and machine learning techniques under development [16,17]. An additional technological intervention feature is the use of videoconferencing. Improving access to weight management advice, through videoconferencing, may assist people in managing their weight, but is yet to be fully evaluated. This study will provide the first test of these digital technologies in people living with obesity in Australia. The study is designed based on key components of effective weight management interventions that include behavioral strategies guided by the (1) capability, opportunity, motivation, and behavior (COM-B) model [18]; (2) the behavior change techniques; and (3) self-monitoring, goal setting, and individually tailored feedback on dietary behaviors [15,19-21]. The objective is to compare the effectiveness of a 1-year digital dietary intervention on body weight reduction and improved diet quality, in adults living with obesity delivered by dietitians in a primary care setting, with a control group.

## Methods

### Study Design

The chat2 (Connecting Health and Technology 2) study is a 1-year randomized controlled trial (RCT). Consenting participants will be randomly assigned (1:1) to an intervention or minimal intervention control group. Figure 1 shows the CONSORT (Consolidated Standards of Reporting Trials) study design. Assessments will occur at 0, 6, and 12 months with the primary outcome assessed at 12 months.

**Figure 1 figure1:**
[figure not shown]
Study design with randomization to two groups: intervention and control groups.

### Consumer Engagement

Engaging with health consumers alongside doctors and health professionals in weight management is a novel and strategic approach to this complex health issue. Using a systems approach provides opportunities for people with lived experience, health professionals, and policy makers to work together to take positive action to address the complex issue of weight management. A systems science group model–building approach was used to develop the East Metropolitan Health Service (EMHS) Obesity Prevention Strategy, to cocreate a shared understanding of the complex issue of obesity, its causes and consequences, and feasible solutions [22]. Health service executives; clinicians; allied health professionals; and representatives from community service providers, government, and nongovernment agencies identified the gap in services for people living with obesity and prioritized action to address this.

This intervention design was developed in partnership with EMHS and informed by the Western Australian Healthy Weight Action Plan, led by the Western Australian Health Department’s partnership with the Western Australian Primary Health Alliance and the Western Australian Health Consumers’ Council [23]. This partnership ensured that peoples’ lived experiences were central to the research. Since 2018, the Western Australian Health Consumers’ Council has conducted several engagement activities to ensure the voices of people with lived experience of overweight and obesity were key drivers of change. A review of weight-management services by this group identified gaps in service delivery, including the lack of supported behavior change programs for weight management, the absence of clear referral pathways, and limited access to a skilled workforce in weight-management care. This study will recruit a panel of health consumers who have lived experiences of overweight and obesity as members of the project advisory board to ensure that their perspectives and voices are considered at all stages of the project. Their role will include reviewing all study materials, including ethics documents, study website design, and recruitment strategies and materials. In addition, the project team and consumers will work to ensure that the trial is respectful, recognizing that participants are likely to have experienced the negative consequences of weight stigma on their health [6].

### Setting

The study setting will target recruitment in the EMHS catchment, 1 of 4 publicly funded health service areas in Perth, Western Australia. EMHS is responsible for the maintenance and improvement of the well-being and health of 725,000 people residing within its catchment, approximately one-third of the population of Western Australia. This is achieved through the provision of an extensive health network including tertiary, secondary, specialist, community, and population health services. The EMHS catchment has the highest prevalence of overweight and obesity in the Perth metropolitan area, where 77% of adults live with overweight or obesity (43% live with obesity) [24,25].

### Recruitment

#### Overview

Participants will be recruited by letters sent to individuals randomly selected from the electoral roll in Perth to provide representation across all socioeconomic status groups. Electoral roll recruitment is a feasible and effective recruitment method previously used by the research team [15]. The mailout will be staggered so that recruitment occurs over 12 to 18 months with a target of 25 participants per month. This will ensure adequate resourcing and staffing for the study. Other recruitment methods will supplement the mail out and will include EMHS hospital sites displaying posters and recruitment postcards; newsletters sent to primary care doctors and practice managers; EMHS and university newsletters; and unaddressed mailbox delivery to residential street points in suburbs located in the EMHS catchment area. Quota sampling will ensure equal numbers between study groups and genders. After receiving the letter of invitation, those who wish to take part in the study will contact the research team by email, mobile telephone (text or voice), or the study website, where they will be directed to read the information statement and consent online, and complete an online screening questionnaire. Computer literacy was not an explicit criterion to be eligible for the study.

To be eligible, participants must be aged 18-65 years, have a self-reported BMI≥30 to ≤45 kg/m^2^, own a mobile telephone with internet access, and be able to attend the study center in metropolitan Perth for all 4 visits. Participants will be excluded on the basis of serious illness or medical conditions including diabetes requiring insulin; medical dietary restrictions (eg, low potassium diet for renal failure); receiving counseling from a dietitian; had or planned to have a surgical intervention for weight management in the next year; severe heart conditions (eg, cardiac failure requiring fluid restriction and a stroke or myocardial infarction in the previous 6 months); severe life-limiting illness receiving palliative treatment (eg, cancer, cirrhosis, and pulmonary disease or heart failure); currently taking or plan to take weight loss medication in the next 12 months; pregnancy or breastfeeding, or planning to become pregnant or breastfeed in the next year; receiving treatment for an eating disorder; or unable to participate in telehealth dietary consultations.

#### Randomization

Block randomization will be used with allocation concealment from the active research team via the use of sealed opaque envelopes. The randomization will be in blocks of 4, with stratification by gender (men, women, and other), where participants will be assigned to either the intervention or minimal intervention control groups (1:1). Sequence generation will be conducted before the commencement of the study by a statistician using a randomization table created in Stata (version 18, StataCorp). The electronic file will be kept in a secure password-protected server by the statistician. Randomization will occur at the second study visit to assign participants to either the intervention or control groups. On opening the randomization envelope, the participant will inform the research staff which group they are allocated to. The trial is unblinded due to the nature of the intervention; it is not possible to blind participants or researchers to the intervention group after allocation.

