#### Dietary Assessment and Analysis

Participants will be provided with access to the mFR app on their mobile device to record their dietary intake at baseline, 6 months, and 12 months (Figure 2) [16,36]. They will be asked to take “before eating” and “after eating” images of all foods and beverages consumed over 4 consecutive days, including 1 weekend day. The mFR app communicates with a dedicated cloud-based server for the storage and processing of images via Wi-Fi or 4G and 5G networks. A fiducial marker is included in the image to allow improved accuracy for quantifying dietary intake [37-39]. The mFR app will be updated regularly in response to operating systems updates (Android and iPhone). Participants will label the content of their images, referred to as mini labels. When the participant starts typing the word, a list of foods will appear where they can select from a list of approximately 800 food and beverage items. These labels link to a food composition database (not visible to the participant) with the food code, detailed description, and energy and nutrient composition [40]. These mini labels will be linked to a code for estimating food group servings to enable a food-based assessment. At the study visit, the research dietitian will review the images with participants through the web and probe for food and beverage items not recorded (Figure 2). The data from the mFR will be entered into a purpose-built Microsoft Access database platform to assess the food group servings.

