#### Diet Quality Scoring

Analysis of the 4-day mFR will be undertaken by the research dietitian, and a food-based diet quality score (DQS) will be calculated (Table 2). In addition to energy reduction, this study will assess diet quality, as there is emerging evidence that diet quality, particularly reduced ultraprocessed foods, have a role in energy balance [41,42]. The 11-component DQS is based on the ADG [26] and adapted from 2 food-based indexes developed for Australian adults [43,44]. The DQS uses a continuous weighting system based on increments of food group servings, or proportions of total intake for behaviors without set recommendations, such as variety of fruits and vegetables. For core food groups, such as fruits and vegetables, the maximum weighting assigned to the item is determined by the ADG-recommended daily servings. To achieve weight reduction consistent with study goals, discretionary foods and beverages will be split into separate components. Reverse scoring is assigned for discretionary (energy-dense and nutrient-poor) foods, sugar-sweetened beverages, and alcoholic beverages, where a maximum score of 10 points is achieved with zero servings. The DQS at baseline and 6 months will be provided to the study dietitians to be relayed to intervention group participants in the video consultations.

**Table 2 table2:** Diet quality scoring calculated from average daily servings based on the Dietary Guidelines for Australia. Total maximum score of 100 points from 11 components.

Item Description	Minimum score	Composite scores	Maximum score
Fruit	0 to <0.5 servings (0 points)	≥0.5 to <1.0 serving (2.5 points) ≥1.0 to <1.5 servings (5 points) ≥1.5 to <2.0 servings (7.5 points)	≥2 servings (10 points)
Vegetables and legumes or beans	0 to <1.0 serving (0 points)	≥1.0 to <2.0 (2 point) ≥2.0 to <3.0 servings (4 points) ≥3.0 to <4.0 servings (6 points) ≥4.0 to <5.0 servings (8 points)	≥5 servings (10 points)
Variety of fruits	0 type (0 points)	1 type (1 point) 2 types (2 points) 3 types (3 points) 4 types (4 points)	5 or more types (5 points)
Variety of vegetables	0 type (0 points)	1 type (1 point) 2 types (2 points) 3 types (3 points) 4 types (4 points)	5 or more types (5 points)
Lean meat, poultry, fish, eggs, nuts, seeds, legumes, or beans (women)	>2.5 servings or <0.5 servings (0 points)	≥0.5 to <1.0 (2 points) ≥1.0 to <1.5 (4 points) ≥1.5 to <2.0 (6 points) ≥2.0 to <2.5 (8 point)	2.5 servings (10 points)

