### Dietetics Training and Consultations

Research dietitians will undertake 8 hours of in-person training, before their consultations with participants. The training will include approximately 2 hours of self-paced, recorded, online training in the dietitian’s own time and 6 hours of online or in-person workshops. The training will include current evidence-based practice for people living with obesity, addressing weight bias or stigma, study design, ethics, mFR technology or study systems, documentation, and fidelity of implementation adherence. Study dietitians will complete online training in motivational interviewing in health care [48]. The behavior change training conducted by the health psychology team will be guided by the COM-B model, and embedded with behavior change techniques [49]. A follow-up booster session will be conducted midway through the intervention. Standard guides will be developed for each of the 8 consultation sessions by the research team. Dietitians will use the consultation guide for each session, record attendance, and contact participants for missed sessions. The style of communication will be consistent with self-determination theory and motivational interviewing principles [15,50,51]. Fidelity of implementation adherence will be guided by a conceptual framework for implementation fidelity [52] (ie, adherence to the guide as prescribed and quality of delivery) and will be assessed for dietitians using measures of fidelity and engagement [53]. Practice management software for allied health professionals [54] will be used to manage appointments; send text appointment reminders; document attendance; record treatment notes; and access anthropometry, DQS, PNQ, and blood test results. Study dietitians will document each of the 8 sessions according to the nutrition care process: nutrition assessment, nutrition diagnosis, nutrition intervention, nutrition monitoring, and evaluation [55,56]. They will also document behavior change techniques implemented according to the COM-B model [20].

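### The statement that researchers cannot be blinded is too broad: coding of stored food images for the diet quality score could be masked, and as written it is not

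*Protocol article*

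**What the plan says.** The Randomization section of the protocol article declares the trial unblinded because of the nature of the intervention and adds that "it is not possible to blind participants or researchers to the intervention group after allocation". It excepts no role and no task.

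The path from image to score is described in two sections:

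- Dietary Assessment and Analysis: "The mFR app communicates with a dedicated cloud-based server for the storage and processing of images". Participants label their own images, and the labels are linked to codes for food group servings. At the visit, "the research dietitian will review the images with participants through the web and probe for food and beverage items not recorded". Then: "The data from the mFR will be entered into a purpose-built Microsoft Access database platform to assess the food group servings".
- Diet Quality Scoring: "Analysis of the 4-day mFR will be undertaken by the research dietitian, and a food-based diet quality score (DQS) will be calculated".

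Two statements bear on who does the counseling. Dietetics Training and Consultations says "Research dietitians will undertake 8 hours of in-person training, before their consultations with participants", and later in the same section calls these staff study dietitians. Diet Quality Scoring says "The DQS at baseline and 6 months will be provided to the study dietitians to be relayed to intervention group participants".

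The Statistical Analysis overview makes 12-month weight change primary and lists DQS change first among the secondary outcomes. The objective names diet quality beside body weight.

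**The concern.** The reason given for not blinding is narrower than the statement it supports. A participant knows whether there are video consultations, and so does the dietitian who holds them. Someone at a desk who turns stored, labelled images into servings need not know.

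The DQS is what the counseling sets out to improve, and its feedback is built around it. If coders know the arm, small judgments about servings can lean one way in one arm. Covariate adjustment cannot remove an error that differs by arm, so a coding difference would be read as a dietary effect. By calling masking impossible, the plan closes off a safeguard that its own data flow allows.

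**Working it through.** **Step 1. Does the stated reason cover each task?**

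| Task | Section | Must the person know the arm? |
|---|---|---|
| Taking part | Randomization | Yes; the participant opens the envelope |
| Counseling | Dietetics Training and Consultations | Yes; only the intervention arm is counseled |
| Image review and probing at the visit | Data Collection Procedures; Dietary Assessment and Analysis | Not in principle, but the participant is present and, at 6 and 12 months, knows the arm |
| Database entry to derive servings, and DQS calculation | Dietary Assessment and Analysis; Diet Quality Scoring | No; images and labels are stored and can be exported under a study ID |

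The impossibility claim fails for the last row. No section of the article describes masked coding, removal of arm labels, or separation of scorers from counselors.

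**Step 2. Can a coding judgment move the score?** Table 2 is stepped. Discretionary foods score 8 points below 0.75 servings and 4 points from 0.75. Vegetables move 2 points per one-serving band. Grains score 10 at 6.0 servings and 0 above 6.0. So a small difference in estimated servings matters for a participant near a cut-point.

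**Step 3. What would a differential lean do to the arm mean?** The document gives no figure. Assume that participants are spread evenly around cut-points about one serving apart, and take the 4-point discretionary step and the 2-point vegetable step. A lean of 0.1 serving then moves about 10% of participants on each item:

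0.1 × 4 + 0.1 × 2 = 0.6 points.

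A lean of 0.3 serving gives 0.3 × 4 + 0.3 × 2 = 1.8 points.

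**Step 4. What would such a shift do to the test?** Inputs: 171 per group (Sample Size section) and a 5% level (Statistical Analysis overview), taken as two-sided. The SD of the DQS comparison and the shift b are assumptions. With no true difference:

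SE = SD × √(2/171); t = b/SE; rejection rate = 1 − Φ(1.96 − t) + Φ(−1.96 − t).

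Example with SD 10 and b = 1: SE = 1.08, t = 0.92, rejection rate 15.2%.

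| Assumed SD | b = 0.5 | b = 1 | b = 2 |
|---|---|---|---|
| 8 | 8.9% | 21.2% | 63.7% |
| 10 | 7.5% | 15.2% | 45.6% |
| 12 | 6.7% | 12.0% | 33.8% |
| 15 | 6.1% | 9.5% | 23.4% |

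The table shows how sensitive the comparison is. It is not an estimate of bias in this trial.

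**The case against.** The strongest reply has three parts. First, the trial declares itself unblinded, and a condensed article may leave coding procedures to the full protocol. Second, coder discretion is limited: participants choose labels from a list of about 800 items, the labels carry serving codes, and a fiducial marker supports quantification. Third, masked coding would leave the larger problem in place, because participants who know their arm still decide what to photograph and label, and the visit interviewer is still unmasked.

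The second and third parts stand, and they limit the gain. The first does not answer the point, because the article does more than stay silent on masking: it says that masking researchers cannot be done.

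Four stronger readings are tempting but unsupported:

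- *The scorers are the counselors.* The training section uses the research dietitian title for those who consult, which suggests this. But the scoring section hands the DQS over to study dietitians, which suggests different people. The text does not settle it.
- *Baseline DQS is contaminated as well.* Data Collection Procedures puts the baseline image interview ahead of allocation in its sequence, and no section dates the scoring. Baseline value is listed only as a possible covariate.
- *Bias of 4 to 6 points.* Adding the Table 2 steps gives this only if every participant sits at a cut-point on both items. Step 3 of the working gives 0.6 points for a lean of 0.1 serving.
- *The statistical analysis must be masked too.* Nothing in this point argues for that.

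**Conclusion.** The point holds in a limited form. The sentence in the Randomization section is right for participants and counseling dietitians and wrong for the coding of stored images. Followed as written, the plan leaves the DQS comparison at risk of an assessor bias that could be avoided at that step. The document gives neither the size nor the direction of this bias. The error rates in the working rest on an assumed SD, an assumed shift, a two-sided 5% test and 171 per group.

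Clinic-measured weight (the primary outcome), DXA and blood results do not pass through this coding step and are unaffected by it. This is a cheap improvement to one secondary outcome, not a threat to the trial's main result.

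**What to change.** 1. In the Randomization section, limit the statement to participants and counseling dietitians, and say that mFR coding and DQS calculation are masked to allocation.
2. Have existing dietitians code servings and DQS from exports that carry a study ID and no arm label, never for participants they counsel, and on the same basis in both arms.
3. Recode stored 6-month records in this way where they have already been scored unmasked. Recruitment ended in August 2024, so 6-month visits were due by about February 2025, before the article appeared in April 2025. The stored images still allow recoding.
4. Lock the DQS file before coders see allocation.
5. Use one scripted probe list, the same for both arms, at the reviews still to be held. The last 12-month visits fall around August 2025.
6. Use one title per dietitian role in Data Collection Procedures, Dietary Assessment and Analysis, Diet Quality Scoring, and Dietetics Training and Consultations, and say whether scorers also counsel.

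The cost is some scheduling, an ID-only export, and the time to recode earlier records. Participants' own reporting bias and the unmasked visit interviews remain, and the report should list both as limitations of the DQS result.
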